## Abstract

**Background:**

Exercise reduced tolerance and breathlessness are common in the elderly and can result in substantial loss in functionality and health related quality of life. Heart failure (HF) and chronic obstructive pulmonary disease (COPD) are common underlying causes, but can be difficult to disentangle due to overlap in symptomatology. In addition, other potential causes such as obesity, anaemia, renal dysfunction and thyroid disorders may be involved.

We aim to assess whether screening of frail elderly with reduced exercise tolerance leads to high detection rates of HF, COPD, or alternative diagnoses, and whether detection of these diseases would result in changes in patient management and increase in both functionality and quality of life.

**Methods/Design:**

A cluster randomized diagnostic trial. Primary care practices are randomized to the diagnostic-treatment strategy (screening) or care as usual.

Patient population: Frail (defined as having three or more chronic or vitality threatening diseases and/or receiving five or more drugs chronically during the last year) community-dwelling persons aged 65 years and older selected from the electronic medical files of the participating general practitioners. Those with reduced exercise tolerance or moderate to severe dyspnoea (≥2 score on the Medical Research Counsel dyspnoea scale) are included in the study.

The diagnostic screening in the intervention group includes history taking, physical examination, electrocardiography, spirometry, blood tests, and echocardiography. Subsequently, participants with new diagnoses will be managed according to clinical guidelines. Participants in the control arm receive care as usual. All participants fill out health status and other relevant questionnaires at baseline and after 6 months of follow-up.

****Discussion**:**

This study will generate information on the yield of screening for previously unrecognized HF, COPD and other chronic diseases in frail elderly with reduced exercise tolerance and/or exercise induced dyspnoea. The cluster randomized comparison will reveal whether this yield will result in subsequent improvements in functional health and/or health related quality of life.

**Trial registration:**

ClinicalTrials.gov NCT01148719

## Background

Reduced exercise tolerance and exercise induced dyspnoea are very common complaints in the elderly, with prevalence rates varying from 20% to 60% [1,2]. In many of the elderly with these complaints heart failure (HF) and/or chronic obstructive pulmonary disease (COPD) may be involved [2]. Multiple causes, however, should be considered, including obesity, anaemia, renal dysfunction and thyroid disorders.

Because of overlap in clinical presentation [3-5], it is difficult to disentangle HF and COPD in the clinical assessment, resulting in both false-negative and false-positive diagnoses of both diseases in primary care [6-10], with subsequent undertreatment and unnecessary drug therapy, respectively. We suspect that especially in the frail, i.e. those prescribed multiple drugs and with multimorbidity, the prevalence of ‘unrecognized’ underlying disease causing reduced exercise is potentially high. For both COPD and HF, but also for other possible underlying diseases such as anaemia and thyroid disorders, effective interventions (i.e. life style interventions and drugs) are available that can improve symptoms, functionality and quality of life and may reduce hospital admissions and mortality [4,11]. Potentially, a substantial beneficial effect in health outcome can be achieved by performing diagnostic tests (screening) in the early course of these diseases.

We designed a cluster randomized trial to examine whether screening frail elderly for HF, COPD, and easy to detect other diseases (such as renal dysfunction, anaemia and thyroid disorders) yields a high proportion of previously unrecognized disease and whether subsequent targeted interventions improves patient outcome. Moreover, we will assess whether such a strategy is cost-effective.

### Key objectives

To determine the yield of screening for previously unrecognized HF, COPD and other chronic diseases (like anaemia, renal dysfunction, thyroid disorders) in frail elderly with reduced exercise tolerance and/or exercise induced dyspnoea.

To assess the effect of the diagnostic screening and subsequent targeted interventions on functional health and health related quality of life after 6 months of follow-up.

To assess the cost-effectiveness of screening and subsequent targeted management.

To identify the most cost-effective combination of screening tests.

## Methods

### Study design

A cluster randomized trial with primary care practices at the unit of randomization, comparing the effects of the screening program (with subsequent targeted interventions in newly detected diseases) compared to usual care on the number of previously unrecognized chronic diseases and on patient outcomes and costs. See Figure 1 for the study scheme.

**Figure 1 F1:**
[figure not shown]
**Study scheme.** S = small (2400 patients), M = medium (4800 patients), L = large (7200 patients), COPD = chronic obstructive pulmonary disease, HF = heart failure, MDS = Minimal Data Set, SF36 = 36 Item Short-Form Health status questionnaire, PE = physical examination, ECG = electrocardiogram, VAS = visual analog scale, MRC = Medical Research Council dyspnoea questionnaire, GP = general practitioner, ^#^other includes cognitive problems (like dementia) and unable to travel to the general practice, ^*^after sending 2 written invitations.

### Study population and recruitment

Patients aged 65 years or over are selected from the electronic medical file of the participating general practitioners (GPs). All participants are recruited by GPs from the catchment area of the ‘network Utrecht care for elderly (NUZO)’. In the Netherlands all citizens are registered with a GP, irrespective of (co)treatment by a specialist, including patients living in a home for the elderly, but except those living in a nursing home or hospice. Our sample can therefore be considered as a representative sample of community dwelling patients aged 65 year or over.

To identify frail elderly we will use the criteria of the ‘transition project Elderly Care Mid Utrecht (Om-U)’; i.e. men or women who are chronically prescribed five or more different types of drugs during the last year, and/or have three or more chronic or life-threatening diseases.

Patients already known with an established diagnosis of COPD (according to the GOLD-criteria [11]) AND also known with established HF (i.e. diagnosed by a cardiologist, backed-up by an echocardiogram [4]) are excluded. Patients who are unable to travel to the surgery of the GP or with severe cognitive problems are also excluded.

The participating GP sends a letter to all eligible frail patients, including an information letter about the study. Patients willing to participate fill out two short questionnaires concerning dyspnoea and exercise tolerance. Those who scored positive on reduced exercise tolerance or had a ≥2 score on the Medical Research Counsel (MRC) dyspnoea scale [12] are included in the study (see Additional file 1 for an overview of the inclusion criteria).

Written informed consent is obtained at the first appointment before any study procedure is undertaken.

### Randomization

Primary care practices are randomly allocated to either the diagnostic screening with subsequent targeted intervention strategy or care as usual. Randomization is considered necessary because we aim to quantify the clinical effectiveness of the strategy (test results followed by targeted treatment initiated by the GP). Cluster randomization is used to avoid contamination of GPs and participants between the two groups, which can occur if randomization is performed at an individual participant level.

Randomization is performed by a computer-based program, using the minimization method. Minimization is based on the size of the general practice (number of enlisted men and women) and ensures that the two arms are balanced in the number of participants.

### Sample size

We estimated that with our diagnostic strategy at least 15% of the population under study would be diagnosed with newly detected HF and/or COPD. These numbers are based on previous diagnostic studies showing that among elderly with COPD 20% had previously unknown HF [6].

To detect a 10% difference between the 2 arms in diagnoses of HF and/or COPD, using an alpha of 0.05, a power of 0.80 and an intracluster correlation coefficient of 0.05[13], 301 participants per arm are needed. Considering a drop-out of 10% we aim to include 400 participants in each arm (total 800). We calculated that around 35 general practices should participate to recruit 800 participants.

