## Results of inclusion

Eighteen general practices are included in the study, 8 were randomized to the diagnostic screening intervention and 10 to the care as usual group.

Of the 11.839 patients aged 65 years or older (16% of all registered citizens) enlist with these practices, 35% met the criteria of frailty. The mean age of the 4142 selected frail patients is 75.6 (SD ±6.9) years and 47% is male. In Table 1 patient characteristics, median number of co-morbidities and medication is given for all selected patients. Of the invited frail patients, 73% responded to our invitation and 30% (1249) was willing to participate. Of those frail patients willing to participate, 33% had no complaints of reduced exercise tolerance or dyspnoea (MRC < 2) and therefore are excluded from the study. Patients excluded because they had no complaints were younger (*p* = 0.04) and more often male (*p* = <0.001) as compared to included patients. Eligible patients who refused to participate (*n* = 3301) were slightly older (*p* = <0.001), but they were comparable on gender (*p* = 0.09) compared to participants.

**Table 1 T1:** Characteristics of all invited frail patients (responders and non-responders)

	**All frail patients**^**#**^	**Patients willing to participate**		**Not willing**^**^**^	**No response**^**>**^
		(*n* = 1249)			
		**Dyspnoea**^*****^	**No dyspnoea**^**<**^		
	(*n* = 4142)				
		(*n* = 841)	(*n* = 408)	(*n* = 1774)	(*n* = 1119)
Age (years), mean (sd)	75.6 ± 6.9	74.6 ± 6.3^·^	73.8 ± 6.1^*‡*^	76.3 ± 7.0^*‡*^	75.9 ± 7.2^*‡*^
Male sex, *n* (%)	1956 (47.2%)	419 (49.8%)^†^	270 (66.2%)^*‡*^	763 (43.0%)^*‡*^	504 (45.0%)^*‡*^
Co-morbidities (number), median (IQR)	3 (3–4)	3 (3–4)	3 (3–4)	3 (3–4)	3 (3–4)
Drugs (number), median (IQR)	5 (4–7)	6 (4–7)	5 (3–6)	5 (4–7)	6 (4–7)

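### The trial passed its 800-participant target with 18 practices instead of about 35, so at the protocol's own ICC the power for 15% v 5% is about 75-77% (68-70% on 16 df), not 80%

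*Protocol article*

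**What the plan says.** The Sample size section of the protocol article expects that "at least 15% of the population under study would be diagnosed with newly detected HF and/or COPD". It sets the target as "To detect a 10% difference between the 2 arms in diagnoses of HF and/or COPD" and concludes: "using an alpha of 0.05, a power of 0.80 and an intracluster correlation coefficient of 0.05[13], 301 participants per arm are needed". It then moves to recruitment, "Considering a drop-out of 10% we aim to include 400 participants in each arm (total 800", and to practices: "We calculated that around 35 general practices should participate to recruit 800 participants". It states neither the control-arm rate nor the number of participants per practice behind the design effect.

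Results of inclusion gives the achieved layout: "Eighteen general practices are included in the study, 8 were randomized to the diagnostic screening intervention and 10 to the care as usual group". The same section reports 395 participants in the screening arm and 446 in the usual-care arm, 841 in all. It does not return to the power.

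**The concern.** In a cluster trial, participants added within a practice contribute less information than added practices. The article prints both the expected and the achieved number of practices, and the second is about half the first. The total of 841 exceeds 800, so a reader will tend to assume that the planned power was met or exceeded. If it was not, a wide interval or a non-significant yield difference could be taken as stronger evidence of no benefit than the design supports.

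**Working it through.** **Inputs from the article.** Alpha 0.05 (taken as two-sided), power 0.80, ICC 0.05, screening-arm yield 15%, difference 10 points, drop-out 10%, 800 participants over about 35 practices planned; 395 in 8 practices and 446 in 10 achieved.

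**Inferred.** Control rate 15% − 10 points = 5%; cluster size (step 1).

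**1. Reproducing the 301.** The unadjusted size per arm with pooled variance is

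n = [1.96·√(2·0.10·0.90) + 0.8416·√(0.15·0.85 + 0.05·0.95)]² / 0.10² = 140.1.

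The implied design effect is 301/140.1 = 2.149. From DE = 1 + (m − 1)·0.05 this gives m = 24.0. As a check, 140.1 × 2.15 = 301.2. At m = 800/35 = 22.9, DE is 2.093 and n is 293, within 3%. Other routes to 301 exist: the unpooled formula needs m of about 24.8 and a continuity-corrected one about 18.6. So 24 is a well-supported inference, not a stated input.

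**2. The planned layout.** With 400 per arm over 35 practices, effective n = 400/2.093 = 191 per arm and power is 90.6%. After 10% drop-out (360 per arm, m = 20.6, DE = 1.979, effective n = 182) it is 89.2%. Exactly 80% corresponds to 602/24, or about 25 practices.

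**3. The achieved layout, normal formula.** Mean m = 841/18 = 46.7, DE = 1 + 45.7·0.05 = 3.29. By arm:

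| | m screening / usual care | DE | Effective n | Power |
|---|---|---|---|---|
| No drop-out | 49.4 / 44.6 | 3.42 / 3.18 | 116 / 140 | 76.7% |
| 10% drop-out | 44.4 / 40.1 | 3.17 / 2.96 | 112 / 136 | 75.5% |

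For the first row, the standard error of the difference is 0.0369 under the null and 0.0380 under the alternative. Then (0.10 − 1.96·0.0369)/0.0380 = 0.73, and Φ(0.73) = 0.767. With unpooled variance throughout, the two rows give 75.0% and 73.7%.

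**4. Allowing for few practices.** With 18 practices there are 16 degrees of freedom between practices. The non-centrality is 0.10/0.0380 = 2.63 and the critical t is 2.12, which gives 69.6%. With 10% drop-out (0.10/0.0386 = 2.59) it is 68.3%.

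**5. Unequal practice sizes.** The article gives no spread of participants per practice, so the CV is an assumption. With DE = 1 + [(1 + CV²)m − 1]·0.05, a CV of 0.3 to 0.5 gives 74% to 70% without drop-out and 73% to 69% with it (normal formula).

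**6. Size needed.** With 10% drop-out the evaluable cluster is 0.9 × 46.7 = 42.05 and DE = 3.05. Then 140.1 × 3.0525 = 428 evaluable, or 428/0.90 = 475 recruited, per arm at this cluster size. That is 428/42.05, or about 10 practices per arm. The arms hold 395 and 446.

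**7. Detectable difference.** Solving steps 3 and 4 for the screening-arm rate that gives 80% power against 5%: 10.5 points without drop-out and 10.8 with it (normal), or about 12 points (t, 16 df).

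**8. Dependence on the ICC.** The normal formula reaches 80% at an ICC of about 0.042 with drop-out. At 0.04 it gives 81-83%, and the t reference 75-76%.

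**9. Drop-out step.** 301/0.90 = 334.4, so 335 per arm. Taken as an allowance for loss alone, 400 corresponds to 1 − 301/400 = 24.75%.

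**The case against.** The strongest reply is that the shortfall is small on the protocol's own method: 3 to 5 points, at assumptions that need not hold exactly. The article says at least 15%, and at 16% v 5% the normal formula gives about 81% even with 10% drop-out. Under Study procedures, the medical files of all participants are searched at six months, so questionnaire drop-out need not remove the yield outcome. The t reference and any CV of practice size are not in the article. It plans a multilevel analysis and already commits to an interval for the yield difference. It nowhere claims that 80% was achieved.

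Much of this stands. It limits the size of the point and supports quoting 76.7% as the upper figure. It does not restore the stated power, which the article ties to an ICC of 0.05 and a 10-point difference. At those values every calculation above falls short.

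Four stronger readings are tempting but unsupported:

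- *That 80% power was conditional on 35 practices.* The article gives 35 as a recruitment estimate, and that layout would have had about 89-91%.
- *That 511 recruits per arm were needed.* This divides 460, which is based on the recruited cluster size, by 0.90. Drop-out also shrinks the cluster, so the consistent figure is 475.
- *That power is only 61-64%.* This needs both the t reference and an assumed CV of 0.5.
- *That 400 is an error to be cut to 335.* The text sets a target and never equates it with 301/0.90; the margin works in the trial's favour.

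**Conclusion.** The concern holds in a limited form. Read against the achieved 18 practices, the stated 80% power is not met at the protocol's own ICC of 0.05. It is about 75-77% on the normal formula that reproduces the 301 and about 68-70% with 16 df, with a further loss if practices differ in size. Against the planned layout, the normal-formula loss is about 14 points. This rests on an inferred 5% control rate and an inferred planned cluster size of about 24. A higher control rate would lower power (about 60-62% for 20% v 10%), but that pair would reproduce 301 only at about 11 participants per practice, which does not fit 800/35. A lower ICC or a yield slightly above 15% would bring the normal-formula figure back to 80%. The shortfall is modest and does not undermine the design, but the reader should not have to discover it.

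**What to change.** Leave the a priori calculation in Sample size as the record of what was planned, and add its two missing inputs: the control rate (apparently 5%) and the assumed cluster size (apparently about 24).

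Beside the practice count in Results of inclusion, add a statement such as: with 18 practices averaging 46.7 participants and an ICC of 0.05, power for 15% v 5% is about 75-77% by the normal approximation (detectable difference 10.5 to 10.8 points), or about 68-70% with 16 degrees of freedom (about 12 points). Keep each power with the detectable difference from the same method. Note that unequal practice sizes lower both powers.

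Add a clause explaining why 400 per arm was chosen when 10% drop-out requires 335, without lowering the target.

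The cost is a few sentences and a less favourable stated power. No extra patients or practices and no change to the analysis are needed.

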COPD, *n* (%)	134 (15.9%)	68 (17.2%)	66 (14.8%)
Asthma, *n* (%)	78 (9.3%)	36 (9.1%)	42 (9.4%)
Mood disorders, *n* (%)	27 (3.2%)	11 (2.8%)	16 (3.6%)
Urinary tract problems, *n* (%)	90 (10.7%)	35 (8.9%)	55 (12.3%)
Osteoporosis, *n* (%)	58 (6.9%)	25 (6.3%)	33 (7.4%)
Malignancies, *n* (%)	51 (6.1%)	18 (4.6%)	33 (7.4%)
Anaemia, *n* (%)	14 (1.7%)	9 (2.3%)	5 (1.1%)
Renal insufficiency, *n* (%)	47 (5.6%)	12 (3.0%)	35 (7.8%)
Thyroid dysfunction, *n* (%)	63 (7.5%)	28 (7.1%)	35 (7.8%)
Osteoarthritis, *n* (%)	212 (25.2%)	126 (31.9%)	86 (19.3%)
Co-morbidities (number), median (IQR)	3 (3–4)	4 (3–4)	3 (3–5)
*Drugs*			
Diuretics, *n* (%)	346 (41.1%)	169 (42.8%)	177 (39.7%)
ACE-i/ARBs, *n* (%)	478 (56.8%)	220 (55.7%)	258 (57.8%)
ß-blockers, *n* (%)	397 (47.2%)	185 (46.8%)	212 (47.5%)
Digitalis, *n* (%)	20 (2.4%)	12 (3.0%)	8 (1.8%)
Oral anticoagulants, *n* (%)	117 (13.9%)	49 (12.4%)	68 (15.2%)
Platelet antagonists, *n* (%)	402 (47.8%)	192 (48.6%)	210 (47.1%)
Treatment for hypercholesterolemia	488 (58.0%)	209 (52.9%)	279 (62.6%)
Anti-diabetic drugs, *n* (%)	223 (26.5%)	109 (27.6)	114 (25.6%)
Treatment for COPD or Asthma, *n* (%)	204 (24.3%)	91 (23.0%)	113 (25.3%)
Drugs (number), median (IQR)	6 (4–7)	5 (4–7)	6 (4–7)

baseline characteristics at selection based on electronic medical fileI Ischemic heart disease includes prior myocardial infarction, angina pectoris, coronary artery bypass grafting, and percutaneous coronary intervention; visual impairment includes cataract, blindness or glaucoma, ACE-i = angiotensin converting enzyme-inhibitor, ARBs = angiotensin receptor blockers.

In total 395 participants were included in the diagnostic screening group and 446 in the care as usual group. The distribution of co-morbidities and drug use of the two arms are shown in Table 2.

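### The stated 301 per arm and 80% power hold only at about 23–24 participants per practice; with the 18 practices reported, power on the plan's own assumptions is about 75–77%

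*Protocol article*

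**What the plan says.** The Sample size section of the protocol article expects that "at least 15% of the population under study would be diagnosed with newly detected HF and/or COPD" and sets out to detect a 10-point difference between arms. It gives "a power of 0.80 and an intracluster correlation coefficient of 0.05[13], 301 participants per arm are needed". For 10% drop-out it raises the target to 400 per arm (800 in total), and it continues: "We calculated that around 35 general practices should participate to recruit 800 participants". It does not state the number of participants per practice used in the calculation, the usual-care rate, or whether alpha is two-sided.

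The Results of inclusion section of the same article then reports: "Eighteen general practices are included in the study, 8 were randomized to the diagnostic screening intervention and 10 to the care as usual group". On participants it says: "In total 395 participants were included in the diagnostic screening group and 446 in the care as usual group". It does not return to the sample size or the power.

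**The concern.** In a cluster trial, the number of participants needed for a given power depends on how many come from each cluster. The trial ended with about half the planned practices and about twice the planned number of participants in each. The total of 841 exceeds the target of 800, so headcount alone suggests that the design was delivered or bettered, while the information in the sample has fallen.

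This is the article's only power statement, and it concerns the difference in yield of HF and/or COPD. If it stands unrevised, a wide interval or a non-significant yield difference will be read against 80% power that the reported design does not have at the plan's own ICC.

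**Working it through.** **Inputs.** From the Sample size section: screening-arm rate 0.15, difference 0.10, alpha 0.05, power 0.80, ICC 0.05, drop-out 10%, 400 per arm, about 35 practices. From Results of inclusion: 395 participants in 8 practices and 446 in 10. Inferred: usual-care rate 0.15 − 0.10 = 0.05, and two-sided alpha.

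**1. Reproducing 301.** Without clustering, using the pooled variance under the null:

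n = [1.96·√(2·0.10·0.90) + 0.8416·√(0.1275 + 0.0475)]² / 0.10² = 140.1 per arm.

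301/140.1 = 2.15. With design effect 1 + (m − 1)·0.05, this gives m = 24.0. The planned 800/35 is 22.9. Rounding n up to 141, m = 23 gives 297 and m = 24 gives 304, while 140 × 2.15 = 301 exactly. Other readings miss at m = 23–24: one-sided alpha gives 234–239, a continuity correction 336–345, 20% v 10% gives 418–428, and 25% v 15% gives 525–538. So 301 depends on a cluster size that fits about 35 practices.

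**2. Design effect as run.**
- Screening: 395/8 = 49.4 per practice; design effect 1 + 48.4·0.05 = 3.42; effective size 395/3.42 = 115.5.
- Usual care: 446/10 = 44.6 per practice; design effect 1 + 43.6·0.05 = 3.18; effective size 446/3.18 = 140.3.
- Overall: 841/18 = 46.7 per practice; design effect 3.29.

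About 140 effective participants per arm are needed, and the screening arm is well short.

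**3. Power by the formula that gives 140.** With effective sizes e₁ and e₂:

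power = Φ[(0.10 − 1.96·s₀)/s₁], where s₀ = √(p̄(1 − p̄)(1/e₁ + 1/e₂)), s₁ = √(0.1275/e₁ + 0.0475/e₂), and p̄ is the mean rate weighted by e₁ and e₂.

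| Design | e₁, e₂ | s₀ | s₁ | Power |
|---|---|---|---|---|
| Planned, 400 per arm, 35 practices | 191.1, 191.1 | 0.0307 | 0.0303 | 90.6% |
| Planned, after 10% loss | 181.9, 181.9 | 0.0315 | 0.0310 | 89.2% |
| As run, all 841 | 115.5, 140.3 | 0.0369 | 0.0380 | 76.7% |
| As run, after 10% loss | 112.1, 135.7 | 0.0375 | 0.0386 | 75.5% |

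For the third row: (0.10 − 1.96·0.0369)/0.0380 = 0.73, and Φ(0.73) = 0.767.

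**4. Sensitivity** (each pair is all 841 / after 10% loss).
- Unpooled variance, normal reference: 75.0% / 73.7%.
- Unpooled variance, t reference on 18 − 2 = 16 df: 69.6% / 68.3%.
- Practice-size coefficient of variation (CV) of 0.4, an assumption, pooled formula: 72.3% / 71.1%.
- ICC 0.04, pooled formula: 82.5% / 81.1%. Power crosses 80% at an ICC of about 0.044 / 0.042.
- 16% v 5%, pooled formula: 82.5% / 81.3%.

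**5. Detectable difference at 80% power** (5% in usual care, ICC 0.05). The pooled formula gives 10.5 points, or 10.8 after loss; the unpooled variance gives 10.8 and 11.0. With an assumed CV of 0.4 the four values run from 11.3 to 11.8.

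**6. Requirement with the practices fixed.** For k practices per arm, n = n₀(1 − ICC)/(1 − n₀·ICC/k). With k = 9, n₀ = 140 gives 140·0.95/(1 − 7.0/9) = 599 per arm, and n₀ = 141 gives 618.

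**The case against.** The Sample size section is a valid prospective calculation. Its figure reproduces, and the sentence on 35 practices is a sound planning statement that recruitment later overtook. The article reports the 18 practices openly. A reader might infer an arithmetic slip in the plan, or a claim that the target was met for 80% power; the documents support neither. The inclusion section gives counts and draws no conclusion about power, and the screening arm, at 395, is itself 5 short of 400.

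The loss is also easy to overstate. The step from 301 to 400 exceeds what 10% drop-out requires (301/0.9 = 334.4, so 335), and that slack absorbs part of the clustering penalty. On the plan's own formula the shortfall against 80% is 3 to 5 points. A reader might infer that power is really 64–70%, but such figures need a t reference on 16 df, unequal practice sizes, or both. The article gives no participant counts by practice, and the size classes in Figure 1 are numbers of registered patients, not trial participants. An ICC slightly below 0.05, or a yield slightly above the stated minimum of 15%, restores 80%.

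Finally, the Statistical analyses section plans a confidence interval for the yield difference and a multilevel approach. If that approach is applied to this comparison, the interval would reflect the larger clusters whatever the stated power.

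All of this stands, and it limits the size of the point. It does not remove it: 0.05 is the ICC the plan chose, and with the plan's stated inputs every variant of the design as run is below 80%.

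**Conclusion.** The concern holds in this limited form: a valid plan became outdated within the same article, and its only power statement was left as it was. At ICC 0.05 and 15% against an inferred 5%, power falls from about 89–91% for the planned 400 per arm to about 75–77% as run. It would be about 68–70% with a t reference for the small number of practices, or about 71–72% with an assumed practice-size CV of 0.4. It would be above 80% if the ICC is about 0.04 or less.

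A reader might also multiply 140 by the design effect of 3.29 and conclude that about 460 per arm is what 18 practices require. That does not follow. 460 participants at 46.7 each need about 10 practices per arm; with 9 per arm the requirement is about 600–620, because adding participants to the same practices enlarges the clusters.

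The conclusion rests on the inferred 5% usual-care rate, two-sided alpha and the back-calculated cluster size, all of which are supported by the fact that together they reproduce 301.

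**What to change.** Keep the 301 and 400 per arm, labelled as the plan, and state the cluster size assumed (about 23–24 per practice, from about 35 practices) and the usual-care rate of 5%, once confirmed. Then add the achieved design:

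- 18 practices (8 and 10), 395 and 446 participants, mean 46.7 per practice;
- design effect about 3.3 at ICC 0.05;
- achieved power about 75–77% for 15% v 5%, with the lower values under a t reference or unequal practice sizes given separately and labelled as such;
- detectable difference at 80% power about 10.5–11 points, or about 11.3–12 with an assumed CV of 0.4.

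Do not give 460 per arm as the requirement for 18 practices.

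The cost is a few sentences and a slightly less favourable stated power. No extra patients are needed, and no procedure or analysis changes.
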